### Statistical analysis

We will perform intention-to-treat (ITT) and per-protocol (PP) analysis of the primary dataset using multivariate and subgroup analysis to evaluate safety, efficacy, OAR and target doses, and treatment strategies, and pair this with CTCAE events, QoL, and PROMs, as appropriate. The primary (safety outcome), toxicity, will be considered in a time-to-event fashion and a complication-free interval and complication-free overall survival will be estimated using the Kaplan-Meier method. Mortality will be presented as a Kaplan-Meier analysis curve. In addition, toxicity will be summarized in a graph as cumulative frequencies of the standardized toxicity levels for each time point. Statistical analysis of effectiveness (secondary analysis) will be performed by comparing the number of VT events, ICD shocks, and ATP events between the six months prior to the six month after the intervention. Effectiveness is described by measures of location and scatter (95% confidence intervals) of the distributions of the features and differences to baseline. In general, confidence intervals will be derived from the score function for proportions and Hodges-Lehmann intervals for medians. The statistical significance level will be two-sided, α = 0.05.

Adverse events will be tabulated by organ or sub-organ system, intensity, and relatedness. During data analysis, relevant stratification criteria are applied to the datasets. Notably, several arrhythmogenic life-threatening entities will be included to determine whether STAR is a ubiquitous treatment or whether certain conditions are more suitable for this innovative approach. VT affects both women and men, irrespective of any stratification criteria.

Missing data and dropouts will be dealt with as independent right censoring. Missing data will be listed, showing reasons for unavailability. Sensitivity analyses of efficacy endpoints will be performed on the per-protocol analysis set defined as the subset of the ITT analysis set who have received protocol treatment and who have no other major protocol deviations thought to impact on the efficacy conclusions of the trial. Only patients who discontinued the study due to consent withdrawal will be replaced with new patients and should get only standard follow-up and no further study-specific follow up.

Statistical analyses will be performed using R version 4.0.2 (The R Foundation of Statistical Computing, Vienna, Austria).

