**Methods:**

Patients with ischemic or non-ischemic cardiomyopathy and recurrent sVA, with an ICD and history of ≥ 1 catheter ablation for sVA will be included. This is a prospective, multicenter, one-arm, dose-escalation trial utilizing the i3 + 3 design, a modified 3 + 3 specifically created to overcome limitations in traditional dose-finding studies. A total of 15 patients will be recruited. The trial aims to escalate the ITV dose from 27.0 Gy to an ITV prescription dose-equivalent level of maximum 35.1 Gy by keeping the PTV prescription dose constant at 25 Gy while increasing the dose to the target (i.e. the VT substrate without PTV margin) by step-wise reduction of the prescribing isodose line (85% down to 65%). The primary outcome of this trial is safety measured by registered radiation associated adverse events (AE) up to 90 days after study intervention including radiation associated serious adverse events graded as at least 4 or 5 according to CTCAE v5, radiation pneumonitis or pericarditis requiring hospitalization and decrease in LVEF ≥ 10% as assessed by echocardiography or cardiac MRI at 90 days after STAR. The sample size was determined assuming an acceptable primary outcome event rate of 20%. Secondary outcomes include sVA burden at 6 months after STAR, time to first sVA recurrence, reduction in appropriate ICD therapies, the need for escalation of antiarrhythmic drugs, non-radiation associated safety and patient reported outcome measures such as SF-36 and EQ5D.

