### Study design

DEFT-STAR is an ongoing single arm, multi-center, phase II, dose escalation trial employing the i3 + 3 design. The design has specifically been created for dose finding studies in radiation oncology. This design has been found to be more robust with regard to statistical operating characteristics than the classical 3 + 3 design [16]. After informed consent is obtained from participants, they will be assigned to a radiation dose group according to the dose escalation simulation.

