### Patient population

Following inclusion criteria are required for participation:

Patients with ischemic as well as nonischemic cardiomyopathies.Implanted ICD or CRT-D.Prior ≥ 1 failed CA (with endocardial ± epicardial approach based on the substrate location and the ECG morphology of clinical VT) procedure to control sustained MMVT using currently recommended mapping and ablation techniques.Patients in whom ablation is not feasible or contraindicated (e.g. LV thrombus or mechanical mitral and aortic valve).MMVT recurrence after CA on optimized antiarrhythmic and heart failure medication.Age ≥ 18 years.IRB-approved, written informed consent as documented by signature.

Exclusion Criteria [17]:

Patients with MMVT who demonstrate:
Acute myocardial infarction.Primary electrical disease (channelopathy).Reversible and treatable cause (e.g., drug-induced or intoxication) of VT that can be adequately addressed otherwise.A target that cannot be safely and precisely defined based on stereotactic radiotherapy accuracy requirements (e.g., anatomical interference from OARs, overlapping prior radiation therapy to the thoracic region).Pregnancy or breastfeeding.Inability to provide informed consent.

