### Outcome measures

The primary outcome of this trial is safety measured by registered radiation associated adverse events (AE) up to 90 days after study intervention. This includes any radiation associated serious adverse event (SAE; at least grade 4 or 5 according to CTCAE v5), in particular death, radiation pneumonitis requiring hospitalization, radiation pericarditis requiring hospitalization and decrease in LVEF ≥ 10% as assessed by echocardiography or cardiac MRI. The secondary outcome measures include efficacy endpoints (i.e. freedom from sustained VT/VF), non-radiation associated safety and patient reported outcome measures (PROMS) as shown in Table 3.

**Table 3 Tab3:** Secondary outcome measures. QOL = quality of life

Efficacy	6-month survival free from electrical storm and incessant VT (binary endpoint) including an initial blanking period of 8 weeks
	Efficacy parameters will be assessed after an initial blanking period of 8 weeks, by comparing the 6 months prior to STAR with the 6 months after treatment, including the 8-week blanking period. All arrhythmic episodes occurring during the blanking period will be collected
	Sustained VT/VF burden as measured by number of post-treatment VT/VF episodes (ECG, ICD readouts). The main analysis will be performed by comparing the 6 months prior to STAR with the 6 months after treatment, which will include an 8-week blanking period
	Time to first sustained VT/VF recurrence as provided by ICD readouts, sustained VT/ICD shock and/or first VT storm
	Reduction of electrical storms and appropriate ATP and ICD shocks
	Need for antiarrhythmic drug use: type and dosages will be collected, and a drug index will be calculated
**Safety**	Overall survival and need for heart transplant or mechanical circulatory support: reported survival and heart transplant rates during follow-up
	Incidence of cardiac arrhythmic mortality or cardiac non arrhythmic mortality
	Non-radiation associated safety, e.g.: Hospitalization for acute heart failure necessitating inotropic therapy and if needed mechanical circulatory support except when other reason is apparent (e.g. acute coronary syndrome) ○ Cardiac tamponade ○ Major stroke or systemic embolism according to current diagnostic standards ○ ICD malfunction necessitating an interventional or operative approach
**Physician-reported and patient-reported QoL**	EQ5D, SF-35, QLQ-5, Treatment decision regret score

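### MMVT recurrence is an entry condition and the baseline is the six months ending at STAR, so regression to the mean can produce part of any before/after fall without a STAR effect

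*Protocol article*

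**What the plan says.** All places are in the protocol article.

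- **Patient population.** The inclusion list requires "MMVT recurrence after CA on optimized antiarrhythmic and heart failure medication". It sets no time limit, no minimum number of episodes and no interval from recurrence to STAR.
- **Outcome measures, Table 3 (Efficacy).** For sustained VT/VF burden: "The main analysis will be performed by comparing the 6 months prior to STAR with the 6 months after treatment".
- **Statistical analysis.** "Statistical analysis of effectiveness (secondary analysis) will be performed by comparing the number of VT events, ICD shocks, and ATP events". The two periods are the same half-years on either side of STAR as in Table 3. Effectiveness is to be described by location, scatter and 95% confidence intervals, with "Hodges-Lehmann intervals for medians". The section also states: "The statistical significance level will be two-sided, α = 0.05". No test is named for this contrast.
- **Study design.** The trial is an "ongoing single arm, multi-center, phase II" study. The abstract says: "A total of 15 patients will be recruited".

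Nothing in the article takes the qualifying recurrence out of the baseline or mentions regression to the mean.

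**The concern.** Patients are selected on the variable that is later compared. The period before STAR is conditioned on containing VT whenever the qualifying recurrence falls within it; the period after STAR carries no such condition. VT episodes vary over time within a patient, so a period chosen because it contained events will on average be followed by a quieter one, even if the treatment does nothing. A single-arm trial has no concurrent group in which that natural fall can be seen and subtracted.

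Table 3 calls this contrast the main analysis of VT/VF burden, and the Background states the aim of identifying a minimal efficacious dose. A fall with an interval excluding zero, or a p-value below 0.05, would easily be read as evidence that STAR works. The mechanism operates with windows of equal length and does not depend on how the 8-week blanking period is handled.

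**Working it through.** **Inputs from the article.** n = 15; single arm; six months before against six months after; two-sided 0.05; MMVT recurrence required for entry.

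**Assumptions, because the article gives no figures.** VT rates, clustering and the timing of the qualifying recurrence are assumed and shown as ranges. The Wilcoxon signed-rank test is inferred from the Hodges-Lehmann intervals.

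**Plan's own figure.** There is none to reproduce. The sample size of 15 is set for dose escalation at an acceptable toxicity rate of 20%. No power, effect size or VT rate is given for this contrast.

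**Step 1: size of the built-in fall.** Let monthly counts be independent and negative binomial with mean m and gamma shape k (smaller k means more clustering). Let the last month before STAR contain at least one episode, and let STAR do nothing.

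- P0 = (k/(k+m))^k is the chance of an event-free month.
- Expected count in the selecting month = m/(1 − P0).
- Expected count before = 5m + m/(1 − P0). Expected count after = 6m.
- Apparent reduction = 1 − 6/(5 + 1/(1 − P0)).

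| m per month | k | P0 | 1/(1 − P0) | Apparent reduction |
|---|---|---|---|---|
| 1 | 0.2 | 0.699 | 3.32 | 1 − 6/8.32 = 28% |
| 2 | 0.5 | 0.447 | 1.81 | 1 − 6/6.81 = 12% |
| 4 | 1 | 0.200 | 1.25 | 1 − 6/6.25 = 4% |

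If monthly rates are autocorrelated and STAR follows directly, the months on both sides share the raised rate. The lower end then drops to about 2%, so the range is about 2-28%.

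**Step 2: chance of a significant fall.** Zero-effect trials of 15 patients were simulated under the Step 1 conditions and tested at two-sided 0.05. The nominal chance of a significant fall is 2.5%. The simulated chance is about 3-19%. As a check on the method, a simulation of six-month counts without selection gave 1.9-2.9%.

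**Step 3: sensitivity to the assumptions.**

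- *At least three episodes in the last month before STAR* (a rule the article does not contain): a significant fall in about 4-61% of null trials.
- *At least one episode anywhere in the six months before:* with population means of 2, 5, 10 and 20 episodes per six months, 10-33%, 4-18%, 4-11% and 2-8% of null trials.
- *The qualifying recurrence as an extra cluster in the baseline:* with λ clusters per six months otherwise, the expected fall is 1 − λ/(λ+1) = 1/(λ+1). That is 50%, 33% and 20% for λ = 1, 2 and 4. A significant fall occurs in 52-73%, 32-49% and 19-27% of null trials.

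**Step 4: what leaving out the qualifying recurrence achieves.** In the extra-cluster model with otherwise stable rates, leaving it out brings the mean change to about zero (−2% to +1%) and significant falls to 1.5-2.7%, the nominal level. With an assumed two months from recurrence to STAR and monthly autocorrelation of 0.8, dropping only the recurrence month still leaves significant falls in about 3-23% of null trials (trigger of at least one episode) or 11-53% (at least three). The correction is therefore partial when patients enter during a prolonged bad period.

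**The case against.** **The endpoint is secondary and partly descriptive.** This stands. The primary outcome is safety, the sample size comes from the toxicity design, and escalation depends only on dose-limiting toxicity. The bias cannot alter any of these. Descriptive reporting does not remove it, however: the shift is in the estimate and its interval, and the section sets a two-sided 0.05 level.

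**The timing is inferred.** This also stands. A reader might infer that every patient's VT has only just recurred, or that patients are enrolled at a cluster, so that the null hypothesis is necessarily false. The inclusion list does not say so. A recurrence more than six months before STAR would lie outside the baseline.

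**The large figures need unstated rules.** A reader might take rejection rates above one half as the expected error. They arise only if entry follows several episodes, or if baseline events are few and the trigger is added to them. Neither condition is in the article. At about 20 episodes per six months with entry on a single episode, the chance of a significant fall is 2-8%.

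**An ineffective dose level could appear effective.** A reader might infer this, but the article states no efficacy test per dose level. The concern applies to the before/after contrast as described.

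**This is a limitation of any single-arm trial, and the detail belongs in the analysis plan.** This holds in part. The absence of a control group is a design choice, and a sensitivity analysis could be left to the SAP. But the article itself fixes the windows, the entry condition and the significance level, and a SAP that kept them would inherit the bias.

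**Conclusion.** The concern holds in limited form. Regression to the mean can produce a fall in VT episodes, ATP and shocks with no STAR effect wherever the qualifying recurrence lies in the baseline. That is likely, because the recurrence is what makes a patient eligible, but it is not documented.

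Under the Step 1 and Step 2 assumptions (n = 15, 1-4 episodes per month, at least one in the last month before STAR, signed-rank test), the built-in reduction is about 2-28% and a significant fall is found in about 3-19% of null trials, against 2.5%. The size cannot be fixed further without VT rates. It grows if entry in practice follows several episodes, or if STAR follows the recurrence by some weeks while rates are autocorrelated. It is small with high, stable rates.

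The point limits what may be concluded about efficacy. It is a cheap improvement to a secondary analysis and no fault in the primary one.

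**What to change.** Change Table 3 (Efficacy) and the Statistical analysis section as follows.

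1. Report the six-month before/after change in VT episodes, ATP and shocks as descriptive, with estimate and 95% confidence interval. State that a p-value below 0.05, or an interval excluding zero, will not be attributed to STAR.
2. Prespecify a sensitivity analysis of episodes per month at risk in which the baseline ends before the qualifying recurrence, leaving out the period from that recurrence to STAR. Report it beside the six-month count.
3. Define the qualifying recurrence as the one that led to referral for STAR and record its date. If the first recurrence after ablation were used instead, the time between ablation and that date would be event-free by construction, and the bias would reverse.
4. State that this removes only part of the bias if patients enter during a prolonged bad period, so agreement of the two analyses does not prove an effect.

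The cost is analysis wording and one recorded date; ICD readouts are already a source for the outcome. No visit, dose or patient number changes. The downsides are a shorter baseline per patient, slightly wider intervals and a somewhat less favourable reduction. The usual six-month count remains available for comparison with other STAR series.

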### Trial organization and coordination

The DEFT-STAR study is an investigator-initiated trial designed by the principal investigators from the Radiation Oncology and Cardiology Departments of the University Hospital Zurich, Zurich, Switzerland. Additional study sites are currently being opened in the second stage of the trial. Participant recruitment, study intervention and follow-up are performed by physicians at the respective Radiation Oncology and Cardiology Departments. Data collection, data management, quality assurance and monitoring are performed by the Clinical Trials Unit, University of Zurich, Switzerland.

### Ethics and study participant safety

The study has been approved by the Cantonal Ethics Committee of Zurich, Switzerland (BASEC 2022 − 00262). This study will be conducted in compliance with the protocol, the current version of the Declaration of Helsinki, ICH-GCP, as well as all national legal and regulatory requirements. An independent data and safety monitoring board (DSMB) including a board-certified radiation oncologist and cardiologist/electrophysiologist has been established. The DSMC will review and evaluate the accumulated study data for subject safety, study conduct and progress, and make suggestions concerning the continuation, modification, or termination of the study. DSMB meetings will be scheduled before the trial start, after enrollment of the first 2 subjects and another 3 subjects, or at least every 6 months. The trial has been registered at clinicaltrials.gov (NCT05594368).

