## Abstract

**Background:**

Stereotactic arrhythmia radioablation (STAR) is delivered with a planning target volume (PTV) prescription dose of 25 Gy, mostly to the surrounding 75–85% isodose line. This means that the average and maximum dose received by the target is less than 35 Gy, which is the minimum threshold required to create a homogenous transmural fibrosis. Similar to catheter ablation, the primary objective of STAR should be transmural fibrosis to prevent heterogenous intracardiac conduction velocities and the occurrence of sustained ventricular arrhythmias (sVA) caused by reentry. We hypothesize that the current dose prescription used in STAR is inadequate for the long-term prevention of sVA and that a significant increase in dose is necessary to induce transmural scar formation.

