While initial trials reported a high immediate success rate, a systematic review of the available clinical data found frequent, sustained ventricular arrhythmia (sVA) recurrences after the index procedure in up to 75% of treated patients within the first year. The commonly employed prescription dose has been 25 Gy either homogeneously or inhomogeneously to the 70–85% isodose line and was shown to maintain a high degree of safety [10]. However, from animal experiments, it is evident that such a dose will not be able to induce transmural fibrosis within the myocardium, which is thought to be necessary for long-term success of VT ablation [11]. A probable explanation for these late recurrences may be the lack of such a transmural fibrosis development in the irradiated myocardium. This would be necessary to homogenize the scar to prevent the development of reentry circuits, the cause of MMVT [12]. Indeed, a mechanism alternative to scar homogenization by which STAR may prevent recurrent sVA has recently been proposed [13].

To date, all studies have focused on initial safety and have not yet explored a possible dose-effect relationship for developing transmural fibrosis. In human trials, to date a maximum dose of 25 Gy was prescribed to the target volume, with inhomogeneity allowed in some instances to amount to a maximum point dose of 33 Gy, which is below the anticipated threshold of 35 Gy for transmural scar formation [10, 14]. Pre-clinical trials have yielded similar findings [15]. Increasing the dose to the cardiac target to induce transmural scar formation is a promising approach to increase the long-term efficacy of STAR.

This study hypothesizes that the underlying mechanism of successful VT treatment is the induction of a homogeneous scar formation within the critical arrhythmic substrate for which a higher radiation dose than the currently applied 25 Gy prescription dose will be necessary. Therefore dose-escalation will lead to a significantly reduced long-term VT recurrence rate compared to the currently applied single dose of 25 Gy. This phase II study aims to identify the optimal dose - i.e. minimal efficacious dose required for successful STAR treatment, while not jeopardizing treatment safety.

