### Sample size calculation

The study is designed as a single arm, multi-center dose escalation trial employing the i3 + 3 design assuming that 15 patients will be treated and an event rate of 20% is acceptable (Fig. 1) [16]. The study will treat 15 patients and escalate the dose up to a maximum level of ITV prescription dose-equivalent level of maximum 35.1 Gy to the 65–90% target encompassing isodose. With the assumption that 15 patients will be treated and a toxicity event rate of 20% ±5 is acceptable, a dose escalation schedule has been simulated [8].

The ITV dose will be escalated from 27.0 Gy to an ITV prescription dose-equivalent level of maximum 35.1 Gy while keeping the PTV prescription dose constant at 25 Gy after each patient if no dose limiting toxicities (DLT) have occurred (E). If a DLT is observed within the first five patients, the dose will not be further increased unless 5 patients were treated at the same dose (S) without occurrence of another DLT in one of these remaining four patients (Fig. 1). In case of a DLT in a second patient at the same dose level a dose de-escalation to the previous lower dose is employed and the current dose will never be used again in this trial (DU). If the ITV prescription dose-equivalent level of maximum 35.1 Gy is reached the remaining patients will be treated at this dose level, until the target cohort of n = 15 is reached. If no radiation associated adverse events occur, dose can be escalated with each recruited patient (i.e. row 0 and columns 1–5 in Fig. 1). The likelihood that dose escalation ensues too quickly with deleterious effects is very small.

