**Fig. 1 Fig1:**
[figure not shown]
Simulation of the dose escalation according to the occurrence of adverse events. Unless an adverse event is registered, dose escalation until the target dose will follow with each patient

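### No DSMB review is guaranteed between dose level 3 and dose level 4, because reviews follow patient count or the calendar while the dose follows the patient sequence

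*Protocol article*

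**What the plan says.** **DSMB timing.** Under Ethics and study participant safety, meetings are "scheduled before the trial start, after enrollment of the first 2 subjects and another 3 subjects, or at least every 6 months". The board makes suggestions on continuing, modifying or stopping the study. No meeting is linked to a dose level.

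**Escalation without toxicity.** Under Sample size calculation: "If no radiation associated adverse events occur, dose can be escalated with each recruited patient". The Fig. 1 caption agrees: "Unless an adverse event is registered, dose escalation until the target dose will follow with each patient".

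**Escalation after one DLT.** In that case "the dose will not be further increased unless 5 patients were treated at the same dose (S) without occurrence of another DLT" in the remaining four patients. A second DLT at a level closes that level.

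**Top level.** Table 2 has four levels. Once level 4 is reached, everyone still to be recruited, up to 15 patients, is treated there.

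**Safety window.** The primary outcome is "safety measured by registered radiation associated adverse events (AE) up to 90 days after study intervention".

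**The concern.** The two early reviews are set by head-count and the dose is set by the sequence of patients and DLTs, so whether a review precedes a given step depends on the path. The step that matters most is entry to level 4. It is the highest dose, and it is where the rest of the cohort goes. An advisory board can usefully suggest a pause or a change to that step only before it is taken. On the most direct paths through the design, the stated schedule does not ensure that the board has seen any level 3 data by then.

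**Working it through.** **Inputs.** Reviews after patients 2 and 5 (Ethics and study participant safety; 2 + 3 = 5). Four levels (Table 2). Escalation rules, target toxicity 20% ± 5 and N = 15 (Sample size calculation). The one-DLT rule is taken to apply at each level, and no replaced patients are assumed.

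**Step 1: reproduce the plan's rule.** The i3+3 rule with interval 15% to 25% works as follows.
- 0 DLTs in n patients: 0 < 15%, so escalate for n = 1 to 5.
- 1 DLT in n patients: for n = 1 to 3 the rate exceeds 25%, but (1 − 1)/n = 0 < 15%, so stay. For n = 4 and 5 the rates are 25% and 20%, inside the interval, so stay.
- 2 DLTs in n patients, n = 2 to 5: the rate is at least 40%, and (2 − 1)/n is at least 20%, so de-escalate.

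This matches the article's description. The article adds that escalation may follow five patients at a level with only one DLT.

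**Step 2: set the patient sequence against the reviews.**

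| Path | First level 3 patient | First level 4 patient | Enrolment-triggered review between | Patients at level 4 if no later DLT |
|---|---|---|---|---|
| No DLT | 3 | 4 | none | 15 − 3 = 12 |
| One DLT at level 1 (patients 1–5 there) | 7 | 8 | none | 15 − 7 = 8 |
| One DLT at level 2 (patients 2–6 there) | 7 | 8 | none | 15 − 7 = 8 |
| One DLT at level 3 (patients 3–7 there) | 3 | 8 | after patient 5 | 15 − 7 = 8 |

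The last row is an exception: there the existing schedule does place a review before level 4. On the DLT-free path, patients 4 and 5 are already allocated to level 4 when the patient-5 review is due.

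**Step 3: other readings.**
- If the three-patient trigger recurs (after 2, 5, 8, 11 and so on), nothing changes on the first three paths. The steps lie between patients 3 and 4, and between patients 7 and 8.
- If the strict i3+3 table governs after one DLT, escalation waits for 1/7 = 14.3% < 15%. Levels 3 and 4 then open at patients 9 and 10, again with no review between.

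**Step 4: the 6-monthly meeting.** No accrual rate is given, so assume steady spacing of d days, counted from the patient-2 review. On the DLT-free path patient 3 enters on day d and patient 4 on day 2d. A meeting at its latest date, about day 183, precedes patient 4 only if 2d ≥ 183, so d ≥ 92.
- d = 60: patient 4 enters on day 120, before the meeting.
- d = 120: the meeting falls between patients 3 and 4, with 183 − 120 = 63 of patient 3's 90 days observed.

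**Step 5: how common the gap is, under assumed DLT rates.** With p the DLT rate at a level, P(pass a level) = (1 − p) + p(1 − p)^4. P(reach level 4) is the product over levels 1–3, minus the product of the three p(1 − p)^4 terms, because 5 + 5 + 5 uses all 15 patients. P(review between levels 3 and 4) = (1 − p1)(1 − p2) × p3(1 − p3)^4.

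At 10% throughout: pass = 0.9 + 0.1 × 0.6561 = 0.96561. P(reach level 4) = 0.9003 − 0.0003 = 0.9001 before rounding of the parts. P(review between) = 0.81 × 0.06561 = 0.0531. The share of level 4 runs without such a review is 1 − 0.0531/0.9001 = 94%.

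| Assumed DLT rates, levels 1/2/3 | P(reach level 4) | P(review between) | No review between, given level 4 |
|---|---|---|---|
| 10/10/10% | 0.9001 | 0.0531 | 94% |
| 5/10/20% | 0.8435 | 0.0700 | 92% |
| 20/20/20% | 0.6854 | 0.0524 | 92% |
| 5/10/40% | 0.6234 | 0.0443 | 93% |

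These figures largely restate the escalation rule: most runs that reach level 4 pass level 3 with one patient. They show that the gap is the usual case, and they measure no harm.

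**The case against.** **The schedule does not cause thin level 3 data.** A reader might infer that level 4 opens on one level 3 patient because of the DSMB timing. It does not. The escalation rule produces that, and an added review leaves it unchanged. This objection stands in full.

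**Prior human exposure.** A reader might infer that level 3 (Dmax 34.5–36.0 Gy) is the first level beyond earlier human doses, since the Background gives a "maximum point dose of 33 Gy, which is below the anticipated threshold of 35 Gy for transmural scar formation". The article does not settle this. The same section describes 25 Gy as given "either homogeneously or inhomogeneously to the 70–85% isodose line and was shown to maintain a high degree of safety". If the isodose is read as a percentage of the maximum, 25/0.70 = 35.7 Gy, inside level 3. Study aim describes the usual dose as prescribed to the 65–90% isodose, and 25/0.65 = 38.5 Gy, inside level 4 (37.5–39.0 Gy). The abstract's "mostly to the surrounding 75–85% isodose line" gives 25/0.75 = 33.3 Gy and fits the lower figure. With these in conflict, the point cannot rest on 33 Gy as a settled maximum.

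**Limited yield.** The board would often be looking at one level 3 patient who is DLT-free to date, and it only advises. That is fair. With an assumed 40% DLT rate at level 3, one patient is DLT-free 60% of the time. The added review is a safeguard of modest strength, and no reduction in toxicity has been shown.

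**Existing protections.** The PTV dose stays at 25 Gy and organ-at-risk doses are limited at every level. The wording on adverse events is also wider than DLT in places, which would slow some escalations and change the Step 5 percentages. The event-free path is the same under either wording.

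**Condensed article.** Ad hoc meetings or dose-level release may be set out in a full protocol or charter that is not shown. But the meeting schedule and the escalation rule are both stated here, and as stated they do not line up. That is a mismatch between two given rules, not a complaint about missing detail.

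**Conclusion.** The point holds in a limited form. On the DLT-free path, and after a single DLT at level 1 or 2, the stated schedule guarantees no DSMB review between the first level 3 patient and the first level 4 patient. A 6-monthly meeting may fall there, depending on accrual. On these paths, 12 or 8 of the 15 patients are then treated at level 4 if no later DLT intervenes.

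This rests on the one-DLT rule applying at each level and on no replaced patients. It needs no assumed DLT rate and no figure for prior human exposure. It does not show that the escalation rule is wrong or that patients would be harmed. It is a scheduling improvement worth considering, not a defect that undermines the design.

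**What to change.** Keep the reviews after patients 2 and 5 and the 6-monthly minimum. Add one review tied to dose level, for example: *The DSMB will review all safety data from levels 1 to 3 before the first patient is treated at level 4. The report will state, for each patient, how much of the 90-day safety window has been observed. A scheduled 6-monthly meeting held at that point may serve as this review.*

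The escalation rules, dose levels and sample size stay as they are. The cost is at most one extra meeting of the existing board and possibly a short pause before the first level 4 patient. On the path with a DLT in patient 3, the patient-5 review sees only part of the five-patient level 3 group, so the new review would also bring that information up to date.
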